8.3 Dissemination of results

At the end of the study, the principal investigator will submit a report on the study and the main outcome. This report will be shared with the national malaria control programme and the Ministry of health. The finding will be presented at Myanmar Research Congress and also at Vector Borne Diseases Control Program Annual Meeting.

The results will be given to study patients at each visit to study clinic. Arrangement will be made with local staff to send the results to those fail to show for follow-up. Health education talks will be given by the Principal Investigator at each supervisory visit.

8.4 Amendments to the protocol

After the protocol has been accepted, no change may be made without the agreement of the principal investigator, the sponsor(s) and the institutional review boards.

9. Ethical considerations

9.1 Approval by the national ethical committee

Before the study, official approval to conduct the study will be obtained from Institutional Ethical Committee, Department of Medical Research (Upper Myanmar) and ERC WHO.

9.2 Informed consent

Patients will be included in the study only if they give informed consent. The consent request, available in English and translated into Myanmar, will be read entirely to the patient. Details about the trial and its benefits and potential risks will be explained. Once any questions have been answered, a signature will be requested on the document (Appendix 10). If the patient is illiterate, a literate witness must sign; if possible, the signatory will be selected by the participant and will have no connection to the research team. Consent statement for the pregnancy test is also required for female participants of child-bearing age who are sexually active.

9.3 Confidentiality

All information on patients will remain confidential and be shared only by the study team. Unique identifiers will be used for computer-based data entry and blood samples. In all cases, the principal investigator will ensure that screening forms, the case report form and the completed identification code list are kept in locked files.

9.4 Health-care services

Free health care throughout follow-up for any illness related to malaria will be provided to the study patients regardless of treatment outcome; this includes any expenses related to hospital admission and to adverse medicine reactions, if required.

When prospective or actual participants are found to have diseases unrelated to malaria, the principal investigator should advise them to obtain, or refer them for, medical care.

Any subject who decides not to participate or cannot be enrolled in the study because they do not meet the criteria, will be referred to the health facility staff. They will be treated with artemether-lumefantrine and followed-up according to the standard of care established by the Ministry of Health. The principal investigator must ensure that this antimalarial drug is available at the health centre.

If a patient is withdrawn from the study before the full course of the treatment is completed, the physician must make all necessary arrangements to provide the patient with the full dose of the medicine currently tested or with a full course of artesunate (4mg/kg stat followed by 2mg/kg/day for 6 days; total dose is 16mg/kg) together with doxycycline (3mg/kg/day) or tetracycline (4mg/kg 4 times daily) also given for 7 days. If available, clindamycin (10mg/kg twice daily for 7 days) is a recommended alternative for these two groups also recommended by the national policy.

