3.6 Exclusion criteria

- presence of signs of severe falciparum malaria according to the definitions of WHO (Appendix 1);
- mixed or mono-infection with another Plasmodium species detected by microscopy;
- presence of severe malnutrition (defined as a child whose growth standard is below –3 z-score, has symmetrical oedema involving at least the feet or has a mid-upper arm circumference < 110 mm);
- presence of febrile conditions due to diseases other than malaria (e.g. acute lower respiratory tract infection, severe diarrhoea with dehydration) or other known underlying chronic or severe diseases (e.g. cardiac, renal and hepatic diseases, HIV/AIDS);
- regular medication, which may interfere with antimalarial pharmacokinetics;
- history of hypersensitivity reactions or contraindications to any of the medicine(s) being tested or used as alternative treatment(s); and
- a positive pregnancy test or breastfeeding (include this criterion only if adults are included);
- unable to or unwilling to take a pregnancy test or contraceptives (for women of child-bearing age);
- previous antimalarial drug intake in the past 48 hours;
- patients presenting with spenectomy.

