4.3 Rescue treatment

If a patient meets one of the criteria for therapeutic failure, ETF and LTF cases, he/she will receive the other artemether-lumefantrine. If the patient is reinfected with another malaria species (*P. vivax, P. malariae or P. ovale*) he/she will receive chloroquine total dose of 25mg base/kg over three days, followed by primaquine 0.25mg/kg/day for 14 days (except for *P. malariae*) according to the current national recommendations.

If the patient vomits the treatment twice, he/she will receive parenteral therapy with artemether IM (80mg/ amp) injection 160mg at 0hrs and l2th hours, and 80 mg at 24th and 48th hours (total = 480mg) plus oral mefloquine (500mg) x 2 doses at 48th and 54th hours and be withdrawn from the study.

With any sign of severe malaria, the study patient will be treated with quinine injection 8 mg/kg of quinine base every 8 hours. Quinine will be given 3 time a day until the patient can reliably take oral medication. The patient will then continue on oral quinine (3x8 mg/kg/day) until they have completed seven days treatment. A seven days course of doxycycline (3 mg/kg/day) will be given also to patients as well as relevant supportive treatments.

5. Evaluation criteria

The study end-point is the classification assigned to a patient. Valid study end-points include: the number of patients parasite positive at day 3, PCT, parasite reduction rate (slope of the log-linear parasite clearance curve), the parasite reduction rate at 48 hours, treatment failure, completion of the follow-up period without treatment failure, loss to follow-up, withdrawal from study, and protocol violation. At all times, the well-being of the patient will take priority over his or her continuation in the study. Secondary end-point is the pharmacokinetic profile of the patients.

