6.1 Screening and enrolment

All patients who meet the basic enrolment criteria (age, fever or history of fever, symptoms of malaria, absence of signs of severe malaria, absence of severe malnutrition, pregnancy) during screening will be assigned a consecutive number and evaluated in greater depth by clinical staff. The screening record form (Appendix 5) will be used to record the general information and the clinical observations on each patient being screened. If the patient meets the clinical criteria, he or she will be examined for parasitaemia. Once the patient meets all the enrolment criteria, he or she will be asked for consent to participate in the study.

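### Section 9.4 gives artemether-lumefantrine to everyone who fails eligibility, including people excluded because they cannot take it and people infected only with another malaria species

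*Protocol*

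**What the plan says.** Section 9.4 defines the group as "Any subject who decides not to participate or cannot be enrolled in the study because they do not meet the criteria". These people are referred to health facility staff, and then: "They will be treated with artemether-lumefantrine and followed-up according to the standard of care established by the Ministry of Health". A supply duty follows: "The principal investigator must ensure that this antimalarial drug is available at the health centre". The only separate provision in 9.4 for people found unsuitable concerns diseases unrelated to malaria, for which the investigator advises or refers.

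Section 3.6 sets the exclusions. Two matter here: "history of hypersensitivity reactions or contraindications to any of the medicine(s) being tested or used as alternative treatment(s", and "mixed or mono-infection with another Plasmodium species detected by microscopy".

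Section 4.3 gives the rescue treatments. For early and late treatment failure it says: "ETF and LTF cases, he/she will receive the other artemether-lumefantrine". For a study patient who acquires another species it says: "he/she will receive chloroquine total dose of 25mg base/kg over three days, followed by primaquine 0.25mg/kg/day for 14 days". It leaves out primaquine for P. malariae and describes the regimen as the current national recommendation.

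**The concern.** One named drug is prescribed for every reason of ineligibility, but some of those reasons bear directly on whether that drug should be given. A person excluded because artemether-lumefantrine is contraindicated would be handed artemether-lumefantrine. A person found at screening to have only P. vivax, P. ovale or P. malariae would receive a treatment different from the one the protocol itself reports as the national regimen for those species.

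The people at stake are those screened but not enrolled. The trial's estimates are not involved.

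**Working it through.** The plan states no figure on this point and no formula applies. The check sets the sections side by side.

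**Group 1: hypersensitivity or contraindication to artemether-lumefantrine**

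1. Section 3.6 excludes on contraindication to the tested drug and also to any drug used as alternative treatment.
2. Section 4.3 makes artemether-lumefantrine the treatment for early and late failures, so it is one of those alternatives.
3. A person with such a contraindication therefore fails the criteria and falls in the group defined by 9.4.
4. Section 9.4 assigns that person artemether-lumefantrine.

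Steps 1 and 4 conflict. Only the part of the exclusion that concerns artemether-lumefantrine is meant. Section 1 lists three national treatments for uncomplicated malaria (artemether-lumefantrine, dihydroartemisinin-piperaquine and artesunate-mefloquine). Section 9.4 names 1 of the 3 and offers no substitute for someone who cannot take it.

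**Group 2: mono-infection with another species**

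1. Section 3.6 excludes it.
2. Section 6.1 places the blood examination before consent: "If the patient meets the clinical criteria, he or she will be examined for parasitaemia". The screening form in Appendix 5 records the species and marks these people ineligible. Screening is therefore built to find them, and they fall under 9.4.
3. Section 4.3 gives two drugs for these species, chloroquine and primaquine, or one (chloroquine) for P. malariae.
4. Section 9.4 names 0 of those 2 drugs, or 0 of 1 for P. malariae.

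The 4.3 sentence is written for study patients who are reinfected. It is used here only as the protocol's own statement of the national regimen, not as a rule for unenrolled people. Section 1 lists national treatments without naming a species, so 4.3 is the species-specific statement. Mixed infection is not part of this point.

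**Search for an exception**

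| Place | What it covers | Covers group 1 or 2? |
|---|---|---|
| 9.4, diseases unrelated to malaria | Non-malarial illness | No |
| Appendix 6, day 0 | Referral for severe malaria or danger signs | No |
| 6.2 | People who decline: facility care under the Ministry standard, no drug named | No; it does not address people who fail the criteria |

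An oral drug is also unsuitable for people with severe malaria or who cannot swallow. That is a lesser matter: 9.4 and Appendix 6 both provide for referral of severe cases, so those two texts do not conflict, and the quinine rule in 4.3 would apply only by analogy.

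**The case against.** The strongest reply is that 9.4 should be read as a whole. It refers these people to facility staff before it names a drug, and the phrase about the Ministry's standard of care can govern treatment as well as follow-up, as it does in 6.2. On that reading artemether-lumefantrine is the default for uncomplicated falciparum malaria, the supply duty is a minimum, and clinicians remain free to choose otherwise. A clinician is unlikely to give a drug against a known contraindication.

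For other species, it can be added that the 4.3 regimen is borrowed from a rule for enrolled patients, that section 1 lists artemether-lumefantrine for uncomplicated malaria without restricting the species, and that nothing in the protocol says the drug fails against those species. For group 1, the screening form mentions contraindication only to the tested medicine, so it would not pick these people out separately.

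Much of this stands as mitigation. It makes harm less likely, and it makes group 2 the weaker case: what is shown there is a departure from the stated national regimen, not an ineffective treatment. It does not remove the defect. The sentence is mandatory, names a drug and is backed by a supply duty for that drug alone. If the standard of care is meant to govern, then for other species the sentence contradicts itself, because 4.3 reports a different national regimen. A safety instruction should not depend on staff setting aside its explicit words. The gap in the screening form does not alter the exclusion in 3.6.

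**Conclusion.** The point holds. Followed as written, 9.4 assigns the wrong treatment to two excluded groups: clearly so for a contraindication to artemether-lumefantrine, and by departure from the protocol's own stated national regimen for mono-infection with another species. The consequence is minor, but it should be fixed.

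The number of people affected cannot be given, because the protocol reports no screening failures by reason. The conclusion rests on two readings: that rescue treatment in 4.3 counts as alternative treatment in 3.6, and that 4.3 correctly reports the national regimen for other species. No endpoint, analysis, sample size or enrolled patient is affected.

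**What to change.** Replace the treatment sentence in 9.4 with one to this effect: people with uncomplicated P. falciparum malaria who can take oral medication and have no contraindication to artemether-lumefantrine will receive it; everyone else will be assessed, treated and followed up by facility staff under the Ministry of Health's standard of care. The second half follows what section 6.2 already says for people who decline. The supply duty for artemether-lumefantrine can stay.

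The cost is a one-sentence edit, processed as an amendment under section 8.4 if the protocol has already been accepted. It adds no procedure and changes nothing for enrolled patients or the analysis.

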3.8 Patient discontinuation or protocol violation

Study patients who meet any of the following criteria will be classified as withdrawn.

- withdrawal of consent. A patient may withdraw consent at any time, without prejudice for further follow-up or treatment at the study site.
- failure to complete treatment, due to:
- persistent vomiting of the treatment. A patient who vomits the study medication twice will be withdrawn from the study and given rescue treatment.
- failure to attend the scheduled visits during the first 3 days; or
- serious adverse events necessitating termination of treatment before the full course is completed. A patient can be discontinued from the study if the principal investigator decides so due to an adverse event of adequate nature or intensity. In this case, information on the adverse event and symptomatic treatment given must be recorded on a case report form. If the adverse event is serious, the principal investigator must notify the sponsor or its designee immediately and follow the reporting procedures described in section 5.3.
- enrolment violation:
- severe malaria on day 0; or
- erroneous inclusion of a patient who does not meet the inclusion criteria.
- voluntary protocol violation: self- or third-party administration of antimalarial drug (or antibiotics with antimalarial activity) (Appendix 2);
- involuntary protocol violation:
- occurrence during follow-up of concomitant disease that would interfere with a clear classification of the treatment outcome;
- detection of mono-infection with another malaria species during follow-up; or
- misclassification of a patient due to a laboratory error (parasitaemia), leading to administration of rescue treatment.

Patients who are withdrawn will nevertheless be followed up until recovery or the end of follow-up, if possible; however, no treatment outcome will be assigned to these patients, and they will be censored or excluded from the analysis. The reasons for discontinuation or protocol violation will be recorded on the case report form.

4. Treatment

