4.1 Antimalarial treatment

The patients will be received artesunate 50 mg per tablet (Guilin Pharmaceutical Company, PRC) 4mg/kg/day for 7 days. Each dose administration will be observed and recorded. The correct drug dosage will be determined from the dosing chart (Appendix 3).

All doses of medicine will be administered under the supervision of a qualified member of the staff designated by the principal investigator. The study patients will be observed for 30 min after medicine administration for adverse reactions or vomiting. Any patient who vomits during this observation period will be re-treated with the same dose of medicine and observed for an additional 30 min. If the patient vomits again, he or she will be withdrawn and offered rescue therapy.

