4.2 Concomitant treatment and medication that should not be used

Fever over 38 °C can be treated with paracetamol or acetaminophen.

During follow-up, if infections other than malaria require the administration of medicines with antimalarial activity, the patient will be withdrawn from the study. Patients given tetracycline as an eye ointment will not be excluded (Appendix 2). Patients will be withdrawn from the study in the case of self-medication or if an antimalarial drug or an antibiotic with antimalarial activity is administered by a third party.

Adverse events requiring treatment can be treated according to local practice. If there is a clinical indication for any additional medication during the course of the study, including medication given to treat an adverse event related to the study medicine, the name of the medicine, the dosage and the date and time of administration must be recorded on the case report form.

The use of herbal remedies during the study should be avoided, and participants should be encouraged to return to the study site for treatment if they feel unwell. If any herbal remedies are taken during the study, this should be captured on the case report form, under ‘study medication administration’.

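### Both treatment options in section 9.4 for patients withdrawn before completing the course contain artesunate, with no exception when artesunate was stopped for a related serious adverse event

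*Protocol*

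**What the plan says.** Three parts of the protocol bear on this patient.

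- **Section 4.1** sets the tested treatment: artesunate "4mg/kg/day for 7 days. Each dose administration will be observed and recorded".
- **Section 3.8** lists the withdrawals. Under failure to complete treatment it includes "serious adverse events necessitating termination of treatment before the full course is completed". For that patient it asks that the event and its symptomatic treatment be recorded and that the sponsor be told. It names no antimalarial.
- **Section 9.4** states the duty of care. The condition and the obligation are "If a patient is withdrawn from the study before the full course of the treatment is completed, the physician must make all necessary arrangements". Two alternatives follow, both named in one phrase: "provide the patient with the full dose of the medicine currently tested or with a full course of artesunate". The second option is dosed at "4mg/kg stat followed by 2mg/kg/day for 6 days; total dose is 16mg/kg" and is given with doxycycline or tetracycline, with clindamycin as an alternative if available.

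Two other sections come close without reaching the case. Section 4.2 says "Adverse events requiring treatment can be treated according to local practice", which concerns the event and not the remaining malaria. Section 4.3 gives rescue regimens, each with its own trigger. The one for severe malaria reads "With any sign of severe malaria, the study patient will be treated with quinine injection 8 mg/kg of quinine base every 8 hours".

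**The concern.** Section 9.4 is triggered by the fact of early withdrawal, whatever the reason. A patient taken off artesunate because a serious event made stopping necessary meets that trigger. Followed to the letter, the rule gives the same drug again.

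This is safe when the event had nothing to do with artesunate. It is unsafe when artesunate is the suspected cause, or when the event has made the drug contraindicated. That patient still has a partly treated falciparum infection and needs an antimalarial, but the only written instruction contains the drug that was stopped. What is at stake is the safety of an individual patient, not any estimate.

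**Working it through.** No trial figure is in question. The one figure in the rule checks out: 4 + 6 × 2 = 16 mg/kg, the total that section 9.4 states. The rest is a reading of every place that could assign this patient an antimalarial.

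**Step 1: does section 9.4 apply?** Its condition is withdrawal before the full course is completed. Section 3.8 classes the serious-event case as exactly that. The wording is mandatory and no reason for withdrawal is exempted. It applies.

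**Step 2: does either option avoid artesunate?**

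| Option in 9.4 | Contents | Artesunate-free? |
| --- | --- | --- |
| Full dose of the tested medicine | Artesunate (4.1) | No |
| Full course of artesunate with a partner drug | Artesunate plus doxycycline or tetracycline; clindamycin as alternative partner | No |

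Result: 0 of 2.

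**Step 3: does section 4.3 supply another regimen?**

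| Trigger in 4.3 | Regimen | Triggered by a serious event alone? |
| --- | --- | --- |
| Early or late treatment failure | Artemether-lumefantrine | No |
| Infection with another species | Chloroquine, then primaquine (no primaquine for *P. malariae*) | No |
| Vomiting the treatment twice | IM artemether plus mefloquine | No |
| Any sign of severe malaria | Quinine plus doxycycline | No, unless the event is itself such a sign |

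Appendix 2 lists artemether and artesunate together as artemisinin derivatives. Quinine plus doxycycline is therefore the only falciparum regimen in section 4.3 without an artemisinin derivative, and it is reserved for severe malaria.

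**Step 4: does anything else fill the gap?**

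- Section 6.2 refers patients with persistent vomiting to the health facility and names no drug.
- Appendix 6 offers alternative treatment only for treatment failure.
- The statement in section 5 that the patient's well-being comes first is about staying in the study and names no drug.

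**Step 5: who is affected?** Section 5.3 has serious events reported whether or not they are thought to be related to the medicine, so some withdrawals under section 3.8 will be for unrelated events, where section 9.4 may be suitable. The problem is confined to patients whose event is suspected to be due to artesunate, or who can no longer take it, and who meet no trigger in section 4.3.

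**Step 6: is efficacy affected?** Section 3.8 assigns withdrawn patients no treatment outcome. Appendix 9 censors them at their last scheduled follow-up before withdrawal in the Kaplan-Meier analysis and excludes them from the per-protocol proportion. What they receive afterwards does not enter either estimate.

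**The case against.** The best defence is that section 9.4 sits under ethical considerations and sets a duty of access: nobody who leaves the study should be left half-treated. Its natural cases are withdrawn consent, missed early visits and enrolment errors, where artesunate remains suitable. A physician who has just stopped artesunate as necessary would hardly read a general clause as an order to restart it. Section 3.6 also excludes patients with known hypersensitivity or contraindications, which narrows the group further.

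Much of this stands, and it is why the point is minor. It does not remove the point. The clause is mandatory and has no exception, and the safe course would require the physician to depart from it. Section 3.6 covers history at entry, not a reaction that first appears on treatment. A patient who develops one is directed to the drug that would have barred enrolment.

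A reader might infer two stronger things that the text does not support:

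- **That section 9.4 offers nothing but artesunate.** The second option adds doxycycline, tetracycline or clindamycin, and Appendix 2 lists all three as having antimalarial activity. What is true is that both options contain artesunate.
- **That the protocol names no other antimalarial.** Section 4.3 names artemether-lumefantrine, mefloquine, quinine, chloroquine and primaquine. What is true is that none is assigned to this patient on the ground of the serious event alone.

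**Conclusion.** The point holds as a minor patient-safety correction. Both options in section 9.4 contain artesunate, no exception is made for a related serious event, and no artesunate-free regimen is assigned to that patient elsewhere in the protocol.

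Its size is 0 of 2 options. The protocol gives no rate for such withdrawals, so no frequency can be stated against the target of 50 patients per site. The amount of artesunate left in the course does not measure the harm: where the drug is contraindicated any further dose is wrong, and where it is not, finishing the course is acceptable.

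The conclusion rests on two conditions: the event is suspected to be related to artesunate or makes it contraindicated, and it is not itself a sign of severe malaria. It does not imply that re-exposure is likely, since clinical judgement would probably prevent it, or that any efficacy result is at risk.

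**What to change.** Add to the withdrawal sentence in section 9.4:

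> except that patients whose artesunate was stopped for a serious adverse event suspected to be related to it, or in whom it is now contraindicated, must not be given artesunate or another artemisinin derivative again; they receive a non-artemisinin regimen, normally the 7-day regimen of quinine (8 mg/kg quinine base three times daily) plus doxycycline (3 mg/kg/day) in section 4.3, or, if that is contraindicated, another non-artemisinin antimalarial chosen by the physician.

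Repeat the same line in section 4.3, so that staff looking up rescue treatment find it there. Leave section 9.4 unchanged for all other withdrawals, including unrelated events after which artesunate is still suitable.

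Two details of the wording matter. The quinine dose must be stated as base, as section 4.3 does. The fallback must be written in, because a serious event may also rule out quinine or doxycycline. The existing rule on route can carry over: "Quinine will be given 3 time a day until the patient can reliably take oral medication".

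The cost is one clause in section 9.4 and the same line in section 4.3. The usual regimen is already prescribed there at these doses, so it adds no new drug or procedure. Under section 8.4 the change needs the agreement of the principal investigator, the sponsor and the review boards.

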5.3 Safety assessment

Safety will be assessed by recording the nature and number of adverse events and serious adverse events. Adverse events will be assessed by direct questioning. An adverse event is defined as any unfavourable, unintended sign, symptom, syndrome or disease that develops or worsens with the use of a medicinal product, regardless of whether it is related to the medicinal product. All adverse events must be recorded on the case report form.

A serious adverse event is defined as any untoward medical occurrence that at any dose:

- results in death, is life threatening;
- requires hospitalization or prolongation of hospitalization;
- results in a persistent or significant disability or incapacity; or
- is a congenital anomaly or birth defect.

‘Life-threatening’ means that the person was at immediate risk for death; it does not refer to a adverse event that might have caused death if it were more severe. ‘Persistent or significant disability or incapacity’ means that a person’s ability to carry out normal life functions is substantially disrupted.

All serious adverse events occurring during the study must be recorded and reported by the principal investigator to the sponsor, regardless of whether the principal investigator considers the events to be related to the investigated medicine.

The investigator will collect information on all people who become pregnant while participating in this study and will record the information on the appropriate form. The person will also be followed to determine the outcome of the pregnancy. Generally, follow-up will be no longer than 6–8 weeks after the estimated delivery date. Any premature termination of pregnancy will be reported. While pregnancy itself is not considered an adverse event or a serious adverse event, any complication of pregnancy or elective termination for medical reasons will be recorded as an adverse event or a serious adverse event. A spontaneous abortion is always considered a serious adverse event and will be reported as such.

6. Study assessment

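### Section 9.4 requires artesunate for every patient withdrawn mid-course, including those stopped for a reaction attributed to artesunate, and Section 4.3 gives them no alternative

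*Protocol*

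**What the plan says.** Section 9.4 sets a general duty that begins: "If a patient is withdrawn from the study before the full course of the treatment is completed, the physician must make all necessary arrangements". What has to be arranged is one of two treatments; the physician is to "provide the patient with the full dose of the medicine currently tested or with a full course of artesunate". The second option is 16 mg/kg of artesunate over seven days together with doxycycline or tetracycline, with clindamycin mentioned as an alternative. Section 4.1 identifies the tested medicine as artesunate, 4 mg/kg/day for 7 days.

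Section 3.8 lists, among the grounds for withdrawal, "serious adverse events necessitating termination of treatment before the full course is completed". It adds: "A patient can be discontinued from the study if the principal investigator decides so due to an adverse event of adequate nature or intensity". Neither statement requires the event to be caused by the drug, and Section 5.3 defines an adverse event "regardless of whether it is related to the medicinal product".

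Section 4.3 gives replacement regimens for four situations: therapeutic failure, infection with another species, vomiting the dose twice, and severe malaria. The last is the only artemisinin-free falciparum regimen: "With any sign of severe malaria, the study patient will be treated with quinine injection 8 mg/kg of quinine base every 8 hours", followed by oral quinine, with doxycycline.

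Section 4.2 adds: "Adverse events requiring treatment can be treated according to local practice".

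**The concern.** Patients withdrawn mid-course for an adverse event meet the trigger in 9.4. If the event is unrelated to artesunate, 9.4 is sound, because the malaria still needs a complete course. If the event is attributed to artesunate, the section directs more of the drug that was just stopped.

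Section 3.6 already treats known hypersensitivity to the tested medicine, or a contraindication to it, as a reason not to enrol. A patient whose first reaction appears on treatment has the same reason not to receive it, but the protocol has no matching provision for that patient.

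The stake is patient safety. Literal compliance re-exposes the patient, while departing from 9.4 leaves the physician without a named regimen to finish treating uncomplicated falciparum malaria. No endpoint, sample size or analysis is involved.

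**Working it through.** This is mainly a comparison of sections; the only arithmetic concerns dose.

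**1. Is the situation foreseen?** Yes. Section 3.8 provides for stopping treatment early because of an adverse event. For such a patient it asks that the event and its symptomatic treatment be recorded, and that serious events be reported. It names no replacement antimalarial.

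**2. Does 9.4 apply to these patients?** Yes. Its trigger is withdrawal before the course is complete, whatever the reason.

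**3. What does 9.4 offer them?** Both of its two options contain artesunate. The clindamycin sentence is loosely worded, but its natural reading is a substitute for doxycycline or tetracycline, so artesunate stays in the regimen.

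**4. Does another section supply a regimen?** The falciparum regimens named for enrolled patients are:

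| Regimen | Situation | Section | Contains an artemisinin |
|---|---|---|---|
| Artemether-lumefantrine | Therapeutic failure | 4.3 | Yes |
| Intramuscular artemether plus mefloquine | Vomiting twice | 4.3 | Yes |
| Quinine plus doxycycline | Severe malaria | 4.3 | No |
| Tested artesunate | Withdrawal mid-course | 9.4 | Yes |
| Artesunate plus antibiotic | Withdrawal mid-course | 9.4 | Yes |

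Four of the five contain an artemisinin (Appendix 2 groups artemether and artesunate as derivatives). The fifth is tied to signs of severe malaria. The remaining regimen in 4.3, chloroquine with primaquine, is for other species. So none of the four situations in 4.3 covers withdrawal for an adverse event. Section 4.2 concerns treating the event, not the malaria.

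**5. How much further artesunate would 9.4 direct?** The planned course is 7 × 4 = 28 mg/kg. If treatment stops after k doses and the first option is read as completing the course, the further dose is 28 − 4k mg/kg:

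| Doses taken (k) | 1 | 2 | 3 | 4 | 5 | 6 |
|---|---|---|---|---|---|---|
| Further artesunate (mg/kg) | 24 | 20 | 16 | 12 | 8 | 4 |

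If the first option were instead read as restarting the course, it would be 28 mg/kg for any k.

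The second option is 4 + 6 × 2 = 16 mg/kg for any k, which reproduces the total printed in 9.4. It opens with a 4 mg/kg dose.

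On every reading, re-exposure is at least one full 4 mg/kg dose. These are nominal doses, before the tablet rounding in Appendix 3.

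**The case against.** The strongest reply is that 9.4 is a duty-of-care clause and not a treatment algorithm. It sits under ethical considerations, next to free care and referral, and its aim is that nobody leaves the study undertreated.

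The protocol does not apply it as an absolute rule either. A patient who vomits twice is withdrawn, usually mid-course, and so falls under 9.4; yet 4.3 gives that patient artemether plus mefloquine, and 6.2 refers such patients to the health facility staff. Section 5 puts the patient's well-being ahead of staying in the study, and 5.1.2 calls for appropriate treatment when clinically indicated. Patients are in hospital for the first 7 days and every dose is supervised, so a physician would have to disregard a recognised reaction in order to re-dose.

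The affected group is a subset of a subset among about 50 patients and could be empty. Whether a reaction to artesunate rules out every artemisinin is also a clinical question that the protocol does not settle.

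Much of this stands. It makes actual re-exposure less likely, and it means the four-in-five count describes what the protocol lists without proving that the other artemisinins are unsuitable. It does not close the gap: none of these provisions names a drug for these patients or qualifies the obligation in 9.4. The vomiting case shows that 9.4 and 4.3 already overlap without a stated order of precedence.

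**Conclusion.** The concern holds. For patients withdrawn mid-course because of a reaction attributed to artesunate, the only written instruction is to give artesunate, and no alternative is named. This is a stated rule that gives the wrong direction in a foreseen situation, not a detail left for later.

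Its reach is limited to that drug-attributed subset. The protocol gives no rate for it, so no number of patients is estimated. For each such patient, the directed further dose is 4 to 24 mg/kg if the course is completed, or 16 mg/kg under the second option.

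The conclusion rests on two readings: that clindamycin replaces the partner antibiotic and not artesunate, and that the general wording on well-being does not override an explicit obligation. Confidence in the textual gap is high. Whether any patient would actually be re-exposed depends on clinical judgement at the site. The point should be fixed for safety; the statistical plan is unaffected.

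**What to change.** - **Section 9.4:** except patients withdrawn for an adverse event attributed to artesunate, or who develop a contraindication to it.
- **Section 4.3:** add a line giving these patients a non-artemisinin regimen. The quinine plus doxycycline already in that section is a candidate; the choice belongs to the sponsor's clinicians.
- **Precedence:** state that 4.3 governs over 9.4 where both apply. This also settles the existing overlap for patients who vomit twice.
- **Attribution:** for serious events, use the suspected-medicine entry already on the Appendix 8 form. For other events, use the investigator's recorded judgement.

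The cost is two or three sentences of protocol text. Both drugs are already named for study patients, so no new drug, procedure, staff or patients are needed.
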